### Participant timeline

The SPIRIT flow diagram of enrolment, pre-study screening, interventions and assessment is provided in Fig. 1.

**Fig. 1 Fig1:**
[figure not shown]
SPIRIT flowchart of study participants

### Sample size

With a total sample size of 172 evaluable patients (IG: *n* = 86; CG: *n* = 86), a medium effect size (d = .44) can be detected in the primary outcome measure between T-CBT and TAU in the planned ANCOVA with a two-sided hypothesis, significance level of 0.05 and statistical power of 90% (when error variance is reduced to 20% by the covariate (baseline depressive symptoms)). With 20% loss-to-follow-up, 216 patients need to be randomised for both ITT and complete-case analysis to reach a power of 90%. Since prior projects suggest that approx. 60% of the patients at risk will meet the inclusion criteria and that again roughly 60% of depressive patients in primary care will participate in the study, 600 patients will be screened for inclusion.

### Recruitment and study procedure

The recruitment process entails two main strategies. In the first instance, study patients will be recruited by 15 participating GPs in the area of Zurich, Switzerland. All patients visiting their GP who are at risk for depression, especially those who present diffuse somatic or chronic somatic symptoms [8] will be screened for depressive symptoms. The GP who has been trained by the study team has two alternative ways of proceeding with study inclusion: a) the GP carries out diagnostics and conducts study enrolment by checking eligibility criteria, obtaining the consent form and handing out the baseline questionnaire; b) the GP alternatively refers the patient directly to the study team: If the patient consents to being contacted, a member of the study team will call the patient and will carry out ICD-10 diagnosis and study enrolment over the telephone. Baseline questionnaire and consent form will be sent via mail.

The second strategy of participant recruitment will be patient-initiated enrolment. Newspaper articles describing the study and the option of participating will be published in regional newspapers and on the homepage of clinical units in Zurich. Patients initiating contact with the study team via telephone will be screened by the study team, who will carry out ICD-10 diagnosis and study enrolment over the telephone. Additionally, patients need to consult their GP and inform them about study participation. Signed consent forms and baseline questionnaire will be sent via mail (see section “consent and confidentiality”). After the study team receives the signed informed consent and baseline questionnaire, patients are enrolled and subsequently randomised.

Patients allocated to the IC will be called by a member of the study team to arrange an appointment between patient and study therapist ideally within 1 week after randomisation. If a patient is assigned to the CG, the first text message will be sent within a week after randomisation. Four months and 12 months after t0, all patients will receive mail from the study team containing the t1-questionnaire and a stamped envelope to return the completed questionnaire. If a patient fails to return the questionnaire, at first one written reminder for filling out the questionnaire will be sent, and, if still unsuccessful, the patient will be reminded by a phone call. For each completed follow-up questionnaire, patients will receive a CHF 25.-shopping voucher.

## Methods: Assignment of interventions

### Allocation

#### Randomisation and sequence generation

All eligible and consenting patients will be allocated randomly to either IG or CG after completion of baseline measurements. The computer-generated randomisation list with block sizes of 10, which contains the enrolment number and an assigned code for allocation to study condition, was prepared by one of the study team members. A research assistant of the unit not involved in the recruitment procedure prepared sequentially numbered opaque envelopes for each enrolment number separately and placed each enrolment number with the corresponding allocation code of the randomisation list in the according envelope. Study allocation will be concealed by a member of the study team (EH) by opening the envelope that corresponds with the enrolment number and by subsequently contacting the patient via telephone in order to declare the allocation result.

## Methods: Data management and analysis

### Data management

Data coding and entry of the paper-based data will be performed manually by a research assistant trained in standardised coding and being supervised by the study coordinator (EH), who will also check accuracy of data entry by conducting sampling inspections. Data will be stored securely and in a pseudonymised manner. Electronic data will be saved on a secure server with access restriction at the University of Zurich including daily backup and accessible exclusively by the study coordinator and principal investigator. After study completion electronic data will be saved on a separate password protected medium (external hard drive), which will be stored together with print data in a lockable cabinet of the Department of Clinical Psychology and Psychotherapy Research. During study trial as well as after completion of the study Principal Investigator and Study Coordinator exclusively have access to the data. In accordance with the national regulations in Switzerland data will be stored for 10 years after termination of the trial. Since all data will be collected in one study site a data monitoring committee was not established.

### Statistical analysis

Data will be analysed according to the CONSORT statement [39]. The primary analysis will refer to the intention-to-treat (ITT) sample that includes all randomised eligible patients. Multiple imputation of missing data will be performed if data required for the primary analysis are missing. For the primary outcome ‘PHQ-9 change in depressive symptoms from t0 to t2’ an analysis of covariance (ANCOVA) with baseline PHQ-9 as covariate and group as fixed effect will be calculated in order to estimate and test the difference between the IG and the CG. The secondary outcomes will be examined in an exploratory manner with appropriate procedures. Sensitivity analyses will be performed by application of an alternative imputation method (last observation carried forward, LOCF), inclusion of further covariates and restriction to complete cases or to the per protocol population (PP sample) consisting of patients without major violations of the study protocol. The decision whether a protocol violation is judged as major will be blindly met by the study team. Interim analyses are not planned. The significance level will be set at 5% (two-sided). Statistical analyses will be carried out with SPSS, Version 23 (IBM Corp., Armonk, NY, USA).

In order to determine the cost-effectiveness of T-CBT, health care utilisation and productivity loss measured with an adapted version of the CSSRI will be monetarily valued by Swiss unit costs to calculate direct and indirect costs. Quality-adjusted life years (QALYs) will be calculated based on the EQ-5D index [40], and the incremental cost-effectiveness ratio (ICER) will be computed. To adjust for baseline differences and to evaluate the uncertainty of the estimates, net-benefit regressions will be conducted and cost-effectiveness acceptability curves will be derived therefrom.

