### Telephone-administered psychotherapy

One increasingly promising approach to overcoming the aforementioned barriers is the application of treatments with the help of remote communication. Telephone and particularly mobile phone is an omnipresent and well-accepted means of communication [13], which has become a reliable tool for managing and delivering care in many areas of the health care system and for a variety of somatic conditions [14, 15]. Telephone-based interventions focusing on mental health have further been proven beneficial and effective in providing CBT for a variety of mental disorders and symptoms, including anxiety disorders in older patients [16], insomnia, health-related quality of life and disability [17] and a variety of conditions where mental health problems co-occurred with chronic somatic disorders. Telephone-delivered psychotherapy – with a special emphasis on CBT (T-CBT) – also shows promising results for the treatment of depression in international meta-analyses [18]. Trials that have thus far investigated this approach for depression in primary care settings have shown lower attrition rates and equivalent improvement in symptom severity at posttreatment compared to face-to-face treatment [19, 20]. Thus, T-CBT could lead to expanded, more flexible, and accessible psychotherapeutic services with the additional option of lowering costs.

However, the majority of trials aim at the reduction of depressive symptoms in patients suffering from chronic and distressing somatic conditions, such as HIV/AIDS, multiple sclerosis and cancer [21–23]. Other studies do not examine T-CBT as a stand-alone treatment for depression; for example, some studies focus on T-CBT in depression care management [24, 25] or as adjunct support in order to ensure adherence to pharmacological treatment. It is also insufficiently clarified whether T-CBT has long-lasting effects on the patients’ mental health and if long-lasting effects would pertain to a less severely depressed patient sample [19].

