## Methods: Participants, interventions, and outcomes

### Study design

The proposed study is a prospective randomised controlled effectiveness trial of short-term T-CBT compared to treatment as usual in primary care patients with mild to moderate depression. Both study arms will receive treatment as usual (TAU). A total of 216 individuals who fulfil inclusion criteria are intended to be randomised in either active treatment or control condition with a 1:1 allocation. Outcomes will be assessed at baseline (t0), at the end of treatment (t1, i.e. 4 months after baseline in CG) and 12 months (t2) after baseline. Table 1 presents a structured summary of the trial by providing items from the WHO Trial Registration Data set.

**Table 1 Tab1:** WHO Trial Registration Data Set

Data category	Information
Primary registry and trial identifying number	ClinicalTrials.gov NCT02667366
Date of registration in primary register	3 December 2015
Sources of monetary or material support	Gottfried and Julia Bangerter-Rhyner-Foundation (Bangerter-Stiftung) and Swiss Academy of Medical Sciences (Schweizerische Akademie der Medizinischen Wissenschaften, SAMW)
Primary sponsor(s)	[name], University of Zurich
Contact for public queries	M.Sc. [name] Department of Clinical Psychology and Psychotherapy Research [name] Switzerland [contact]
Contact for scientific queries	[name]. [name] Department of Clinical Psychology and Psychotherapy Research [name] Switzerland [contact]
Public title	Telephone-Intervention/Information for Depression (TIDe)
Scientific title	Effectiveness and cost-effectiveness of a telephone-based cognitive-behavioural therapy in primary care for mild to moderate depression
Countries of recruitment	Switzerland
Health condition(s) or problem(s) studied	Mild to moderate depression
Intervention(s)	Telephone-delivered short-term cognitive-behavioural therapy
Key inclusion and exclusion criteria	Inclusion criteria: Age ≥ 18 years, mild to moderate depression according to ICD-10, PHQ-9 > 5 and ≤15, able to fill in questionnaires, German language Exclusion criteria: suicidality or suicidal tendency, currently or in last 3 months in psychotherapeutic treatment, chronic depression or dysthymia, severe depression, psychopharmacological medication that is not stable for 3 months prior to enrolment.
Study type	Randomised-controlled superiority trial
Date of first enrolment	January 2016

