### Study interventions

#### T-CBT (intervention group)

The intervention group (IG) will receive T-CBT in addition to TAU, which is a short-term telephone-delivered psychotherapy. The therapy programme is a manualised cognitive-behavioural therapy (CBT) consisting of one initial face-to-face appointment and 8–10 subsequent telephone sessions (+ 2 optional booster sessions) with the study therapist. Telephone contacts will take place on a weekly and – after the first four sessions – on a bi-weekly basis and will last 3–4 months in total. Each telephone contact should last between 30 and 40 min and will be audio recorded for the sake of assessing treatment integrity and evaluating treatment process variables.

The therapy programme is a translated and culturally adapted version of the programme *Creating a balance* developed in the US [24, 27]. The German version (“Ins Gleichgewicht finden”) has been evaluated as part of a stepped care trial [28], i.e. was part of a complex intervention of stepped care which was evaluated as a whole. For the proposed study, the manual has been adapted slightly according to special characteristics and cultural features of the Swiss population (especially adaption of the case studies, e.g. using typical Swiss expressions and names).

The manualised programme comprises the central components of CBT for depression: the first part of the programme focuses on behavioural activation and the subsequent chapters centre upon strategies of cognitive restructuring. Further essential treatment elements are psycho-education and relapse prevention. After a maximum of 10 sessions there is the option of adding up to two booster sessions for enhancing long-term maintenance of treatment effects. Patients receive a workbook which they work with independently between sessions and then discuss materials with the telephone therapist. Moreover, since regular symptom monitoring (PHQ-9) is part of the telephone treatment, patients learn to monitor themselves concerning their depressive state. Despite the strong structure and guidance provided by the therapist, the programme has a strong self-help character and thus requires patients to delve into the contents and acquire skills themselves with support of the therapist.

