### Outcomes and measures

#### Outcome assessment

Outcomes will be assessed via self-report paper-pencil questionnaires at baseline, post-intervention and follow-up, which will be sent to the patient via mail. The primary outcome of effectiveness refers to a change in symptom severity from t0 (baseline) to t2 (12 months after baseline), measured by the German version of the PHQ-9.

Secondary outcome parameters will include the change in depressive symptoms from t0 to t1, response defined as a 50% reduction in the PHQ-9 value from t0 to t1, remission defined as <5 points in the PHQ-9 at t2 and t1, and relapse defined as ≥5 points in the PHQ-9 at t2 following remission at t1. Further secondary outcome is change in health-related quality of life (HrQoL) assessed by the SF-12. Furthermore, the incremental cost-effectiveness of T-CBT compared to TAU will be analysed based on (direct and indirect) costs and quality-adjusted life years (QALYs) observed within the 12-month follow-up period.

In addition to outcome measures, there will be an assessment of structural and process variables. For the IG, these will entail amount and duration of telephone contacts as well as contents of the sessions. Additional assessments take place at the beginning of each telephone session in order to monitor symptom severity and measure therapist ratings regarding the therapeutic alliance between patient and therapist. Therapists’ and patients’ acceptance of and satisfaction with T-CBT will be assessed with a self-constructed questionnaire based on instruments from the study team’s prior research.

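### LOCF, the alternative imputation named for the 12-month PHQ-9, assumes persistence for patients lost after t1 and so is a poor robustness check of a durability question (minor)

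*Protocol article*

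**What the plan says.** All references are to the protocol article.

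- **Endpoint (Outcome assessment).** "The primary outcome of effectiveness refers to a change in symptom severity from t0 (baseline) to t2 (12 months after baseline"), measured with the PHQ-9. The Hypotheses section likewise places the primary comparison at 12 months.
- **Assessment times (Study design).** After baseline, outcomes are taken "at the end of treatment (t1, i.e. 4 months after baseline in CG) and 12 months (t2) after baseline". Recruitment and study procedure has the two follow-up questionnaires posted to all patients at 4 and 12 months. Therapy "will last 3–4 months in total" (T-CBT section), so t1 falls at about its end.
- **Missing data (Statistical analysis).** For the primary analysis, "Multiple imputation of missing data will be performed if data required for the primary analysis are missing". The sensitivity analyses are "application of an alternative imputation method (last observation carried forward, LOCF"), and then "inclusion of further covariates and restriction to complete cases or to the per protocol population (PP sample").
- **Expected loss (Sample size).** "With 20% loss-to-follow-up, 216 patients need to be randomised".
- **Durability as the open question (Telephone-administered psychotherapy).** "It is also insufficiently clarified whether T-CBT has long-lasting effects". Relapse between t1 and t2 is also a defined secondary outcome.

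**The concern.** A sensitivity analysis for missing data should show whether the conclusion survives a different and plausible assumption about the patients who were not seen. For someone who returned t1 but not t2, LOCF assumes that nothing changed over the 8 months after therapy ended. The trial asks about exactly those months, and the protocol expects some patients to relapse in them.

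For someone who returned neither questionnaire, LOCF assumes no change since baseline. The result therefore depends on when patients stopped responding, not on a stated assumption about how they fared.

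What is at stake is interpretation. If multiple imputation and LOCF agree, the paper may present this as support for a lasting effect, although LOCF has built persistence in for part of the sample.

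**Working it through.** **Inputs from the protocol:** 216 randomised, 1:1 (108 per arm); 172 evaluable (86 per arm); 20% loss; d = 0.44; two-sided 5%; 90% power; ANCOVA on baseline PHQ-9.

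**Assumptions, because the protocol gives no figure:** the t1 effect (d_t1), the true t2 effect (d_t2), and q, the share of patients lost at t2 who did return t1. Unless stated otherwise, loss is equal in both arms and unrelated to outcome. Positive d favours T-CBT.

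**1. The plan's own figure.** With residual variance 0.8 after adjustment, n per arm = 2 × (1.96 + 1.2816)² × 0.8 / 0.44² = 86.8, so 87 per arm or 174 in total, against 172 stated. Power at 86 per arm is 0.897. Inflating for loss, 86 / 0.8 = 107.5, so 108 per arm and 216 in total. The factor 0.8 is the reading that reproduces the stated size, and it is used below.

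**2. What LOCF estimates.** Of all patients, 80% contribute their observed t2 score. A share 0.2q contributes the t1 score. A share 0.2(1 − q) contributes baseline, where the expected group difference is zero. So:

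expected LOCF effect = 0.8 × d_t2 + 0.2 × q × d_t1

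bias = 0.2 × (q × d_t1 − d_t2)

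LOCF favours T-CBT only when q × d_t1 exceeds d_t2.

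**3. Results with d_t1 = 0.44.**

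| True d_t2 | q = 1 | q = 0.5 | q = 0 |
|---|---|---|---|
| 0 | 0.088 | 0.044 | 0 |
| 0.22 | 0.264 | 0.220 | 0.176 |
| 0.44 | 0.440 | 0.396 | 0.352 |

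The first row overstates the effect unless q = 0. The second overstates it, is unbiased, or understates it, according to q. The third understates it whenever q is below 1.

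**4. Rejection by LOCF when d_t2 = 0.** LOCF treats all 216 scores as observed, so SE = √0.8 × √(2/108) = 0.1217.

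- q = 1: 0.088 / 0.1217 = 0.72, giving about 11.2% two-sided rejection instead of 5%.
- q = 0.5: 0.044 / 0.1217 = 0.36, giving about 6.5%.

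Simulation with ANCOVA and assumed correlations of 0.45 to 0.6 gives similar values: 10.5% to 11.4% at q = 1 and 6.4% to 7.2% at q = 0.5.

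**5. Unequal loss.** Suppose there is no effect at any time, symptoms return by 0.3 to 0.5 SD after t1 in both arms, every lost patient has t1, and 30% of the IG but 10% of the CG are lost. LOCF then shows 0.3 × 0.2 = 0.06 to 0.5 × 0.2 = 0.10 SD in favour of T-CBT. With the loss rates exchanged the sign reverses.

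**6. A case where the check should warn.** Let d_t1 = 0.44, q = 1, and d_t2 = 0.10 among patients still observed, with lost IG patients a further 0.5 SD worse. The true overall effect is 0.10 − 0.2 × 0.5 = 0. Multiple imputation under missing at random gives 0.10 SD. LOCF gives 0.8 × 0.10 + 0.2 × 0.44 = 0.168 SD. Simulated rejection was 12.5% and 28%. Here LOCF errs in the same direction as the primary analysis, and further.

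**The case against.** The strongest reply is that LOCF is not the primary analysis. Multiple imputation in the ITT sample is, and LOCF stands beside complete-case, covariate-adjusted and per-protocol analyses. This stands. A reader might infer that naming LOCF threatens the primary result. The document does not support that: the threat to the primary result is informative dropout, which would exist whether or not LOCF were listed.

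Second, a reader might infer that LOCF tilts the check toward T-CBT. That holds only when q × d_t1 exceeds d_t2. The protocol gives neither q nor a t1 effect, and it offers booster sessions intended to maintain benefit, so fading cannot be presumed. The direction must be left open.

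Third, the rejection rates in step 4 are for LOCF alone. If loss is unrelated to outcome, the primary analysis keeps its 5% error, and both analyses cannot reject together more often than that. Simulated joint rejection, with complete cases standing in for multiple imputation, was about 2.4% to 3.0%. This also stands. False reassurance of the kind in step 6 needs dropout related to outcome.

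Fourth, a reader might infer that no planned analysis allows for worse outcomes among lost IG patients. A condensed article cannot establish this, since such analyses are commonly left to an SAP, which is not shown. What remains open to criticism is the method the article does name.

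None of these replies makes LOCF a suitable check for a question about persistence.

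**Conclusion.** The point holds as a minor one. For patients lost after t1, LOCF assumes the 8-month persistence that the trial is meant to test. For patients without t1, it assumes no change from baseline. It is an uninformative robustness check that can appear to confirm persistence.

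Under the planned 20% loss and an assumed t1 effect of 0.44 SD, the error runs from +0.088 SD (effect gone by t2, every lost patient has t1) to −0.088 SD (effect fully kept, none has t1). These figures rest on the assumed t1 effect, on q, and on equal loss unrelated to outcome. The textual fact is certain; the direction and size of the bias are not. The primary estimate, the significance level and the sample size of 216 are unaffected.

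**What to change.** In Statistical analysis, replace LOCF with a delta-adjusted multiple-imputation sensitivity analysis. Add a fixed penalty, for example 0, 1, 2 and 3 PHQ-9 points, to the imputed t2 scores in the IG only. Repeat the ANCOVA for each penalty and report the value at which the conclusion changes. With 20% of IG scores imputed, these penalties move the group difference by 0.2 × penalty, that is 0, 0.2, 0.4 and 0.6 points, so the assumption and its effect are both visible to the reader.

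This uses the imputed datasets already planned for the primary analysis. It needs no change to design, data collection or sample size. The cost is a little more analysis and reporting.

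A control-based version, in which missing IG scores are imputed from the CG distribution, is an optional extra. It needs a separate imputation run.
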